#### Visit at treatment end (T2)

After the last session, questionnaires are sent to the parents for completing them at home and bring them back at the T2 visit. Children and parents will complete the same self-report questionnaires as at T1, but for the HiPIC and the satisfaction questionnaires (only at T2), and BRIEF (only at T1) (Table 1). During the T2 visit, parents are interviewed by a clinician to assess the child’s overall functioning (C-GAS). This visit does not exceed 30 min. If needed, questionnaires can also be completed with the help of a researcher. The SDQ-Teacher questionnaire is again completed by the child’s teacher

#### Visit at month 6 post-treatment (T3)

This follow-up visit determines whether the intervention effects persist at month 6 after the intervention end. Children and parents will be interviewed by a clinician to complete the C-GAS. Before the visit, they will complete the same self-report questionnaires as at T1 (at home) (Table 1). This visit takes approximately 30 min.

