### Intervention description {11a}

#### Cognitive Behavioral Therapy group

The CBT group is based on the manualized program “How to improve anger and frustration management” (“Mieux gérer sa colère et ses frustrations,” [59]). The CBT program « Mieux gérer sa colère et ses frustrations » is based on the Anger Coping Program [51]. The program has demonstrated effectiveness with a reduction of aggressive behaviors and an improvement of self-esteem [50]. Similar programs based on cognitive behavioral therapy showed that these interventions allow improving aggressive behaviors [82].

This program has been originally designed for impulsive and aggressive children at school [56]. Afterwards, it has been adapted to children with ADHD and has been evaluated several times. A first study carried out on children with Opposant Defiant Disorder (ODD) showed that parents reported a reduction of externalizing behaviors in their child. Teachers highlighted significant improvement of self-control, but no difference on externalizing behaviors. A second study showed satisfaction and feasibility of this program in children with ADHD. Families reported a generalization of techniques in daily life, a reduction of conflict during homework and a better self-control in their child with ADHD [57]. In a study, this CBT program was combined with a parent management training (« Mieux vivre le TDAH à la maison », [60]) and showed an improvement of social skills in children with ADHD, a reduction of parental stress, and a better parent-child relation [58].

Sessions of the CBT program have been developed from social cognitive model of anger and aggression [47] in order to explain that the way by which the child evaluates the situation as well as own emotional and physiological reactions generate aggressive responses. In this model, parents play a crucial role in maintaining and reinforcing of aggressive behaviors in children as well as in characteristics of their child [52].

The program consists of 1-h sessions (one per week; 15 in total) led by a psychologist and a caregiver (nurse or educator) both trained in the management of behavioral disorders and ADHD. They also have in-depth knowledge of CBT that they practice regularly.

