**Assessments:**				
Structured clinical interview (K-SADS-PL)		X		
*Parent-rated measures*				
Child Behavior Checklist (CBCL)		X	X	X
Strengths and Difficulties Questionnaire (SDQ-Par)		X	X	X
Behavioral Rating Inventory of Executive Function (BRIEF)		X		X
Hierarchical Personality Inventory for Children (HiPIC)			X	
Kidscreen-27		X	X	X
Parental Quality of Life and Developmental disorder in their children (Par-DD-Qol)		X	X	X
Parenting Stress Index 4^th^ edition (PSI-4-SF)		X	X	X
Beck Depression Inventory-II (BDI-II)		X	X	X
*Child-rated measures*				
Kidscreen-27		X	X	X
*Teacher-rated measures*				
Strengths and Difficulties Questionnaire (SDQ-Teacher)		X	X	X
*Clinician-rated measures*				
*Children’s* Global Assessment Scale (C-GAS)		X	X	X

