#### Pretreatment visit (T1)

Participants and their parents will participate in a visit to determine their eligibility (Enrollment, Table 1). Then, the T1 visit takes approximately 2 h, because the diagnostic interview (K-SADS-PL) is carried out systematically with the parents to confirm the diagnosis of ADHD and the presence of comorbidities. During this visit, parents are interviewed by clinicians for clinical ratings of their child’s overall functioning impairment (C-GAS). Children and parents will also complete self-report questionnaires (see Table 1). A questionnaire (SDQ-Teacher) is completed also by the child’s teacher. This questionnaire is either given to parents who will directly transmit it to the teacher, or sent by mail.

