#### Secondary outcomes

The trial includes several secondary outcome measures, and also the clinician ratings of impairment (C-GAS). Moreover, parents complete questionnaires about their child to evaluate:
Global functioning (SDQ, C-GAS)Executive functions (BRIEF)Personality traits (HiPIC)Quality of life (Kidscreen-27).

Parents also complete questionnaires to evaluate:
Parental stress (PSI-4-SF)Parental depression (BDI-II)The impact of their child disorders on the quality of family life (Par-DD-Qol).

Secondary outcomes include also teacher-report measures of the child’s global functioning (SDQ-Teacher), and child-report measure of the quality of life (Kidscreen-27).

The study objectives are to evaluate the CBT program impact on the socio-communicative capacities, emotional and behavioral self-regulation capacities, quality of life of child and family, overall functioning of child, and parental stress/depression in the short term (intervention end) and also at month 6 post-intervention. Finally, the personality profiles of children with ADHD will be analyzed to determine whether there are common personality traits in children with ADHD and ED.

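### The T3 visit text omits the SDQ-Teacher that Table 1 schedules, and testing its raw T1–T3 change will, for many children, subtract scores given by two different teachers

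*Protocol article*

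**What the plan says.** All references are to the protocol article.

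- **Table 1, Assessments:** the only entry under teacher-rated measures is the SDQ-Teacher, marked at T1, T2 and T3.
- **Pretreatment visit (T1):** "A questionnaire (SDQ-Teacher) is completed also by the child’s teacher". The delivery route follows: "This questionnaire is either given to parents who will directly transmit it to the teacher, or sent by mail".
- **Visit at treatment end (T2):** "The SDQ-Teacher questionnaire is again completed by the child’s teacher".
- **Visit at month 6 post-treatment (T3):** "Before the visit, they will complete the same self-report questionnaires as at T1 (at home". The subject is the children and parents. The sentence ends with a pointer to Table 1. No teacher form and no route to a teacher are mentioned.
- **Secondary outcomes:** "Secondary outcomes include also teacher-report measures of the child’s global functioning (SDQ-Teacher".
- **Outcomes:** change in the SDQ from baseline to month 6 is a secondary criterion, and change from baseline to the end of the intervention is exploratory.
- **Statistical methods for the primary and secondary outcomes:** changes in secondary outcomes from T1 to T2 and to T3 are compared between arms by a Z test. Linear regression is held back for the case where the groups turn out not to be comparable.

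No section says which teacher rates at T3, or how a change of teacher is to be treated.

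**The concern.** Two things are at issue.

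First, the visit texts are uneven. At T1 and T2 the article describes the child and parent forms, cites Table 1, and then gives the teacher form its own sentence. At T3 it stops after the child and parent forms. Someone working from the T3 text alone has no prompt to send the teacher form.

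Second, the planned contrast for this outcome is a raw change over a span close to a school year. If a different teacher fills in the T3 form, the subtraction mixes change in the child with the difference between two raters. The SDQ-Teacher is the only measure in Table 1 that comes from outside the family and the study clinic, and under *Who will be blinded* parents and children know the allocation. Avoidable noise in this measure weakens a useful cross-check on the parent-rated results.

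**Working it through.** **1. Visit texts against Table 1**

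| Time point | Table 1 | Visit text names the form | Visit text gives a route |
|---|---|---|---|
| T1 | marked | yes | yes (through parents or by mail) |
| T2 | marked | yes | no |
| T3 | marked | no | no |

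The gap is in the T3 text. The schedule itself is consistent. *Outcomes* has primary and secondary outcomes assessed at all three times, *Secondary outcomes* includes the teacher form, and the case report form content for the six-month visit covers primary and secondary outcome data.

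**2. Length of T1 to T3**

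Inputs: 15 weekly sessions (*Cognitive Behavioral Therapy group*: "The program consists of 1-h sessions (one per week; 15 in total"; the same number in the theater arm), and T3 at six months after the end, taken as 26.1 weeks. One month is taken as 4.345 weeks.

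- No wait and no breaks: 15 + 26.1 = 41.1 weeks; 41.1 / 4.345 = 9.5 months. Counting only the 14 intervals between sessions gives 40.1 weeks, or 9.2 months.
- *Sequence generation* says randomization waits until both groups can be filled, but gives no length. Assuming a wait of 0 to 8 weeks and breaks of 0 to 4 weeks, the upper end is 8 + 15 + 4 + 26.1 = 53.1 weeks, or 12.2 months.

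The article's own figure, under *Explanation for the choice of comparators*, is about one year to the end of the study. The upper part of this range reproduces it.

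**3. What that implies for the rater (illustration only)**

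The article gives no term dates and no T1 dates. Assume a school year from 3 September to 5 July (306 possible start days) with T1 spread evenly over it.

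- T1 and T3 in the same school year: 19/306 = 6% at 41.1 weeks; 0% at 45.1 weeks or more.
- T1 and T2 in the same school year: 201/306 = 66% at 15 weeks; 145/306 = 47% at 23 weeks.

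Under this calendar a change of school year between T1 and T3 is the usual case. The figures move with the assumed calendar and with batch starts, so they show direction and do not estimate the number of children affected.

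**4. Cost of the raw change**

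Let the teacher score have variance 1 at both times and let r be the T1–T3 correlation, which is lower when the raters differ. Then:

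- variance of the change = 2(1 − r)
- variance of the T3 score adjusted for T1 = 1 − r²
- ratio, adjusted to change = (1 − r²) / [2(1 − r)] = (1 + r)/2

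| Assumed r | Change | T3 alone | T3 adjusted for T1 | Ratio |
|---|---|---|---|---|
| 0.1 | 1.80 | 1.00 | 0.99 | 0.55 |
| 0.3 | 1.40 | 1.00 | 0.91 | 0.65 |
| 0.5 | 1.00 | 1.00 | 0.75 | 0.75 |
| 0.7 | 0.60 | 1.00 | 0.51 | 0.85 |

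The adjusted comparison has the smaller variance at every r below 1, so the gain does not depend on knowing how many children change teacher. Below r = 0.5 the raw change is noisier than the T3 score on its own. At r = 0.3 it would need 1.40/0.91 = 1.54 times as many children for the same precision.

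**The case against.** The strongest case on the other side has several parts.

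- **The form is scheduled.** A reader might infer from the T3 text that the month-6 teacher data will be missing. The documents do not support that: Table 1, *Outcomes*, *Secondary outcomes* and the case report form content all provide for it, and the T3 sentence itself points to Table 1. In a single-hospital trial this is an incomplete description in a condensed article. This objection stands.
- **It is not the only school-rated change.** T1–T2 teacher change is also collected and tested. This stands.
- **The calendar is assumed.** Neither the share of children who change teacher nor the suggestion that some T3 visits fall in school holidays (with the same worry for the Kidscreen-27 school domain) can be settled from the article. This stands. What remains is the span of 9.5 months to about a year, which makes a different teacher likely for many children.
- **Noise, not bias.** One CBT and one theater group start together, randomized 1:1 and stratified by school level, so changes of teacher should fall alike on both arms. A reader might infer a biased comparison, but nothing in the documents supports that. Nor does the article say that teachers are blind, so the form should not be presented as a protected outcome.
- **Imputation is planned.** It deals with absent forms. It does not deal with a form completed by another teacher.
- **Same-teacher analyses are debatable.** Whether the teacher is the same at a later visit is known only after randomization, and T1–T2 change is exploratory in the plan. This stands, and it limits the fix below.

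**Conclusion.** The point holds in a limited form. The T3 visit text is out of step with Table 1 and should be aligned with it. The stated Z test on raw T1–T3 change suits this outcome poorly, because two teachers will often be involved and their difference enters the change score as noise. On an assumed r of 0.3 the variance is 1.40 against 0.91 for the adjusted T3 score; over r from 0.1 to 0.7 the adjusted variance is 55% to 85% of that of the change. These ratios rest on equal variances at T1 and T3 and on assumed correlations, since the article gives none for the SDQ-Teacher.

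The effect is confined to one secondary outcome. The parent-rated CBCL primary outcome and the sample size of 68 do not depend on it.

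**What to change.** 1. **Analysis.** For the SDQ-Teacher, compare arms on the T3 score by linear regression with the T1 score as covariate, in place of the Z test on raw change. This needs no new data and costs one line in the analysis plan. The article says analysis starts only once all visits are done, so the line can be fixed before then.
2. **T3 text.** Add one sentence naming the SDQ-Teacher and how it reaches the teacher, to match Table 1.
3. **Recording.** Where possible, note on each teacher form its date and whether the rater is the same teacher as at T1, and use this for description or a sensitivity analysis only. According to *Trial status* the article was submitted after recruitment ended, so for forms already returned this may be only partly recoverable.

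The T1–T2 change in children who kept the same teacher should not become the main teacher contrast. It selects on something that happens after randomization and would displace the month-6 criterion that the plan sets.

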### Sample size {14}

As ED in children with ADHD has been only recently studied, it is difficult to find literature data for calculating the number of subjects required (particularly for assessing the changes in the “Aggressive behaviors,” “Anxiety/Depression,” and “Attentional Problems” scores of the CBCL scale).

The study by Masi et al [54]. reported a change in the “Aggressive behavior” score of the CBCL from 68.3 to 65.5 in the context of the non-comparative evaluation of an intervention similar to the one assessed in the present trial. The standard deviation of the score at the baseline was 5.4.

By making the reasonable assumption of a slightly more effective intervention than what reported by Masi et al [55]., a CBCL score of 65 in the intervention group and 69 in the control group, with a common standard deviation of 5.5, can be expected at month 6 post-intervention. To highlight such a difference with a power of 80% and an alpha risk of 5%, 31 subjects per group need to be included. By increasing this number by 10% to take into account participants lost to follow-up, the total number of subjects to be included in the study is 68 (34 per group).

### Recruitment {15}

Patients will be recruited at the Child Psychiatry and Neuropediatric units of Montpellier University Hospital. Information leaflets will be distributed by psychiatrists and may be posted electronically to families. Researchers will give presentations on this trial to the general public and mental health professionals.

## Assignment of interventions: allocation

### Sequence generation {16a}

After verification of the eligibility criteria, family’s information, and consent signature, each participant will be randomized. Intervention allocation will be done using a computer-based random number generator. Randomization will be performed as soon as the number of participants is reached to start a session (one CBT group and one TBI group) with a 1:1 ratio.

Randomization will be stratified by school level (primary vs middle school) and severity of psychopathological disorders using the CBCL A-A-A score. Children will be divided in groups according to their school level (< 11 years, and 11–13 years of age).

The investigator in charge of the study assessments is blinded to the group allocation.

### Concealment mechanism {16b}

Randomization is done by the Department of Medical Information of Montpellier University Hospital using the Capture System software (Clinsight).

### Implementation {16c}

If participants are interested in the trial, psychiatrists or pediatricians give information and enroll them. Then, participants are contacted by telephone by the investigator. The psychologist informs about the study, verifies that families are aware of the implications of participation in a trial, and proposes an appointment for the initial evaluation. She verifies that children are motivated and willing to participate in the trial. Indeed, often, parents register their child without asking their opinion, while it is important that they are involved and motivated in order to benefit from the intervention. After the initial evaluation, participants are assigned to an intervention group by the research coordinator after randomization.

## Assignment of interventions: blinding

### Who will be blinded {17a}

The research psychologist who performs the baseline and outcome assessments will be blind to the treatment conditions. Due to the nature of the interventions, it will not be possible for the researchers who administer the intervention to remain blind. Researchers who administer the intervention will not be involved in the collection of the outcome data to avoid bias in measuring results.

Given the study design, parents and children are not blind and are informed about the group allocation after randomization.

### Procedure for unblinding if needed {17b}

There is no procedure for revealing a participant’s allocated intervention during the trial, because it is not a protocol targeting a pharmacological treatment. Therefore, it did not seem necessary to provide circumstances for and an unblinding protocol.

## Data collection and management

### Plans for assessment and collection of outcome data {18a}

Outcome data will be collected by a research psychologist with a case report form (CRF). Data will be verified by supervised psychology students to detect errors in the collected data. Finally, data will be verified by a methodologist who will process all statistical data.

The case report form includes the following:
Initial inclusion: inclusion and non-inclusion criterion; date of signed consent, inclusion in the study and randomization; data of all questionnaires, sociodemographic characteristics (marital status, socioeconomic status, education attainment), and clinical characteristics of children (age, sex, school level, comorbid disorders, drug treatments, rehabilitation therapy) and parents (somatic and psychiatric pathologies);Participations in intervention: at each session, we will note the date, the presence or absence of parents and child, the reason for absence, and the name of present parent (mother, father or other);Visit at the end of intervention (T1): data of primary and secondary outcomes; life events, introduction or modification in drugs treatment; side effects;Visit at 6 months after intervention (T2): data of primary and secondary outcomes; life events, introduction or modification in drugs treatment; side effects.

It is possible to provide French version of case report form on a request of the Editorial Office.

#### Primary outcome

##### Child Behavior Checklist (CBCL [3];)

The CBCL is a 118-item parent-completed questionnaire to measure emotional and behavior problems in 4- to 18-year-old children in the past 6 months. Parents rate each item as 0 (not true), 1 (somewhat or sometimes true), or 2 (very true or often true). The CBCL includes eight syndrome scores: Anxious/Depressed, Withdraw/Depressed, Somatic Problems, Social Problems, Thought Problems, Attention Problems, Rule Breaking, and Aggressive Behavior. A computer program calculates the *T*-scores for each scale. Raw scores are converted to gender- and age-standardized scores. A *T*-score of 50 indicates average functioning and standard deviation is every 10 points.

The objective of the primary outcome is to assess the effectiveness of the CBT program on the “Aggressive behavior” score (i.e., primary outcome) of the CBCL A-A-A. The CBT program should allow reducing aggression.

The “Aggressive behavior” sub-score contributes to the CBCL-DP and “Deficient Emotional Self-Regulation” (CBCL-DESR). The two profiles are the sum of the CBCL “Anxious/Depressed,” “Attention Problems,” and “Aggressive Behavior” (A-A-A) syndrome *T*-scores [3]. The CBCL-DESR is present when the sum of the CBCL A-A-A scores is ≥ 180, but below 210 (*T*-scores > 60). The “Dysregulation Profile” is present when the sum of the CBCL A-A-A scores is ≥ 210 (2 SD; *T*-scores > 70). These profiles represent a continuum of the emotional and behavioral dysregulation severity [14, 55]. They allow defining an ED phenotype and are a risk marker of a persisting deficit of self-regulation of emotion and behavior [40]. CBCL-DP and CBCL-DESR allow identifying a group of children with disruptive behavior [4] and at risk of severe dysfunction [30, 40, 79]. The CBCL-DP and CBCL-DESR profiles are associated with higher risk of comorbidities [27, 40, 55], hospitalization in psychiatry services [27], and development of inappropriate personality traits [67] in adulthood. The CBCL-DESR profile is a predictor of increased risk of opposition defiant disorder, conduct disorder, and anxiety disorders [79]. The CBCL-DP predicts high risk of mood disorders during adolescence [54].

#### Secondary outcomes

The trial includes several secondary outcome measures, and also the clinician ratings of impairment (C-GAS). Moreover, parents complete questionnaires about their child to evaluate:
Global functioning (SDQ, C-GAS)Executive functions (BRIEF)Personality traits (HiPIC)Quality of life (Kidscreen-27).

Parents also complete questionnaires to evaluate:
Parental stress (PSI-4-SF)Parental depression (BDI-II)The impact of their child disorders on the quality of family life (Par-DD-Qol).

Secondary outcomes include also teacher-report measures of the child’s global functioning (SDQ-Teacher), and child-report measure of the quality of life (Kidscreen-27).

The study objectives are to evaluate the CBT program impact on the socio-communicative capacities, emotional and behavioral self-regulation capacities, quality of life of child and family, overall functioning of child, and parental stress/depression in the short term (intervention end) and also at month 6 post-intervention. Finally, the personality profiles of children with ADHD will be analyzed to determine whether there are common personality traits in children with ADHD and ED.

##### French version of the Strengths and Difficulties Questionnaire (SDQ-Fr, Goodman, 1997)

SDQ-Fr is a standardized questionnaire completed by parents or teachers that allows a brief emotional and behavioral screening of 2- to 17-year-old children and adolescents (http://www.sdqinfo.com). The SDQ-Fr includes 25 items divided in 5 subscales with 5 items/each to assess emotional symptoms, conduct problems, hyperactivity/inattention, peer relationship problems, and prosocial behavior. The questionnaire is completed on paper in 5–10 min.

The SDQ-Fr allows obtaining a “dysregulation profile” (SDQ-DP). It is a combination of two items from the Emotional symptom subscale (“Many worries, often seems worried,” “Often unhappy, down-hearted or tearful”), two from the Conduct problem subscale (“Picked on or bullied by other children,” “Steals from home, school or elsewhere”), and one from the Hyperactivity/Inattention subscale (“Restless, overactive, cannot stay still for long”). A study suggested that children with ADHD and SDQ-DP display more angry reactions and are less capable to control their anger [22]. The SDQ-DP allows identifying children with ADHD at risk of severe difficulties in overall functioning. A study showed that SDQ-DP is a predictor of developing psychiatric disorders in the next 4 years [91].

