### Outcomes {12}

Primary and secondary outcomes will be evaluated in the two groups (TBI and CBT) at the inclusion visit (baseline), at the end of intervention, and at month 6 after the end of the intervention.

The primary judgment criterion is the variation of the “Aggressive behaviors” score of the CBCL between baseline and month 6 post-intervention. The initial evaluation will be on outcomes at month 6 post-intervention; because we hypothesize that the effectiveness of such programs is observed several months after their end. Usually, it takes time for children and parents to assimilate and routinely implement the new techniques and also to observe the intervention benefits in the daily life. This will allow also assessing whether the beneficial effects of the interventions are maintained in the long term.

Secondary judgment criteria include also the variation between baseline and month 6 post-intervention of the CBCL A-A-A score, CBCL-Internalizing and CBCL-Externalizing scores, KIDSCREEN-27, Parental Quality of Life and Developmental Disorder (Par-DD-Qol), Children’s Global Assessment Scale (C-GAS), Parenting Stress Index-Short Form, 4^th^ edition (PSI-4-SF), Beck Depression Inventory-II (BDI-II), and Strengths and Difficulties Questionnaire (SDQ) and the SDQ-dysregulation profile (SDQ-DP).

Exploratory analyses will be realized and will concern the variation of primary and secondary judgment criteria between baseline and at the end of the intervention. Exploratory analyses will be realized to identify possible mediators concerning personality traits on therapeutic effects (response to treatment at T2).

Other data will be collected during the initial visit: presence or absence of psychiatric disorders in children using the K-SADS-PL diagnostic tool, sociodemographic data, anamnestic data, and medication history. Pharmacological treatments will be recorded at each visit because the introduction of a new drug or the modification of posology may influence the research outcomes. Indeed, ADHD usual treatment effectively reduces ED ([28, 46, 86]; Gamli et al., 2018 [97];). The Hierarchical Personality Inventory for Children (HiPIC) will be completed at the end of the intervention to limit the duration of the initial visit.

Means, standard deviations or frequencies, median and percentages will be calculated in order to describe sociodemographic and clinical variables of the sample as well as primary and secondary outcomes.

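### The item list for the SDQ dysregulation profile, a secondary endpoint, puts a being-bullied item under conduct problems; item and subscale do not fit and should be checked before scoring

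*Protocol article*

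**What the plan says.** Under Outcomes {12}, the secondary criteria for change from baseline to month 6 post-intervention include the "Strengths and Difficulties Questionnaire (SDQ) and the SDQ-dysregulation profile (SDQ-DP".

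The section on the French SDQ, under Secondary outcomes, describes a 25-item questionnaire with five subscales of five items each, intended "to assess emotional symptoms, conduct problems, hyperactivity/inattention, peer relationship problems, and prosocial behavior". It then builds the SDQ-DP item by item:

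- Emotional: "It is a combination of two items from the Emotional symptom subscale (“Many worries, often seems worried,” “Often unhappy, down-hearted or tearful".
- Conduct: "two from the Conduct problem subscale (“Picked on or bullied by other children,” “Steals from home, school or elsewhere".
- Hyperactivity: "and one from the Hyperactivity/Inattention subscale (“Restless, overactive, cannot stay still for long".

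The section gives no item numbers, response range, weights or cut-off for the SDQ-DP. On anger it reports one finding from a cited study: "A study suggested that children with ADHD and SDQ-DP display more angry reactions and are less capable to control their anger".

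**The concern.** The section assigns items to subscales by name, and one assignment does not fit. Being picked on or bullied is something that happens to the child. It is not the child's own conduct, and a subscale for difficulties with peers is named a few lines earlier.

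The definition can therefore be followed in two ways. An analyst who goes by the item wording scores the bullying item. An analyst who goes by the label looks for a second conduct item and scores a different one. The two would obtain different values for a named secondary endpoint at every visit where the SDQ is completed.

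A second observation points the same way. Background and rationale {6a} describes emotional dysregulation through features that include irritability, aggression and tantrums, yet none of the five listed items is about anger, temper or aggression.

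**Working it through.** The plan gives no figure to reproduce here. The check compares passages and counts items.

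**1. Item count.** 2 (emotional) + 2 (labelled conduct) + 1 (hyperactivity/inattention) = 5.

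**2. Each item against its label, by wording alone.**

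| Item (paraphrased) | Label in the article | Fit |
|---|---|---|
| Worries | Emotional | Fits |
| Unhappy, tearful | Emotional | Fits |
| Bullied by other children | Conduct | Does not fit; describes victimization by peers |
| Steals | Conduct | Fits |
| Restless, overactive | Hyperactivity/inattention | Fits |

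One of five items does not match its label, and it is one of the two labelled conduct. The article does not print the full key linking items to subscales, so this is a strong inference from wording and not a proven contradiction.

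**3. The two possible errors.**

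- *The item is wrong and the label right.* A different item belongs in that place, and scoring as written uses a wrong one.
- *The label is wrong and the item right.* The five items stand and the score does not change. Only the description needs correcting.

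**4. Share of the score if the item is wrong.** The article states no weights, so these are assumptions:

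- five items weighted equally: 1/5 = 20%;
- three domains weighted equally, and items equally within each: 1/3 × 1/2 = 1/6, about 17%.

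These are shares of the score. They do not estimate a bias in the comparison between groups.

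**5. Content.** Items on anger, temper or aggression: 0 of 5. For comparison, the CBCL profile described under Primary outcome is a sum of three syndrome scores, one of which is Aggressive Behavior. If the bullying item stands where another conduct item belongs, that could explain the gap, but the documents do not establish it.

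**6. Reach.** Table 1 schedules the parent and teacher SDQ at T1, T2 and T3, so any item error would recur at each visit. The article does not say whether the SDQ-DP is derived from the parent form, the teacher form or both.

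**The case against.** The strongest reply is that this is descriptive text in a condensed article. The score may be computed from the instrument's own key, with the mismatch no more than a slip of translation or copying. That is possible, and if only the label slipped, no result changes. The sentence is nevertheless the only item-level definition in the document, and its parts do not agree. A check is justified whichever part is wrong.

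Several stronger readings are tempting, and the objection to each stands:

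- A reader might infer that the score as listed fails to measure its stated construct. The construct is a dysregulation profile with emotional, conduct and hyperactivity items. Anger appears only as a correlate reported by a cited study, and a profile can correlate with anger without containing an anger item.
- A reader might infer that a CBT effect on outbursts would go undetected. The primary outcome is the CBCL Aggressive Behavior score, and Outcomes {12} also lists the CBCL A-A-A and Externalizing scores and the SDQ itself.
- A reader might take the SDQ-DP as the only dysregulation measure outside the CBCL. The BRIEF section describes a behavioral regulation index that includes emotional control, and Objectives {7} states a hypothesis on the BRIEF behavioral index.
- A reader might say that neither program addresses bullying. The CBT description covers resolving conflicts and dealing with the anger of others, and the TBI description covers prosocial skills, so peer victimization could plausibly change.

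**Conclusion.** The concern holds in a limited form. The article defines a named secondary endpoint at item level, and one of the five items does not fit the subscale to which it is assigned. Either the item or the label is very probably wrong, and the document cannot show which.

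The effect ranges from none, if only the label is wrong, to one wrong item in five. The 20% figure for the latter rests on equal item weights, which the article does not state. The absence of an anger or aggression item is a further reason to check the list; it is not evidence that the score is invalid. The matter is confined to the SDQ-DP and leaves the primary outcome, its analysis and the sample size untouched.

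**What to change.** Before the analysis:

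1. Check the five items against the SDQ scoring key and against the source that defines the SDQ-DP.
2. List them by item number in the analysis plan, and correct the SDQ section so that each item agrees with its subscale.
3. Score the SDQ-DP at all visits from the corrected list.

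This does not presume which part is wrong. The cost is one line in the analysis plan and one check of the scoring program. No new data are needed, because all 25 items are on the questionnaire; this assumes that answers are kept item by item, not only as subscale totals. The timing allows it: Trial status reports that patients were still taking part in groups, and Interim analyses {21b} places the analysis after all visits are complete.
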